### Data collection

Each participant’s medical history, details of their foot assessment and comorbidities will be recorded in Qualtrics software [69], either directly into Qualtrics or from a paper-based case report form (CRF) to Qualtrics. This information will be obtained from the treating high-risk foot service with the participants’ consent. Participants’ preferences and adherence-related information will also be recorded in the same software for analysis following a similar data entry process. Plantar pressure data and shoe wear period data will be collected at each appointment with the researcher. Persons will be de-identified/anonymised before sending the data to the statistician.

### Data management

Each participant will receive a study enrolment number, which will be used on an electronic spreadsheet. This way, participants can be re-identified by utilising the study enrolment number when further data collection or clarification is required. Once collated, data will be non-identifiable.

Data management and storage will be maintained in line with the National Health and Medical Research Council’s (NHMRC) ethics requirements [70]. Any hard copy, such as the participant’s signed consent form, CRF’s will be scanned and stored in the form of an electronic copy, and hard copies will be disposed of in a locked confidentiality bin. Electronic data will be stored on a password-protected computer with an up-to-date version of Trendmicro Maximum Security antivirus software. For each site, a Research Data Management Plan (RDMP) form will be maintained. Initial data will be stored at Southern Cross University (SCU)-approved data storage system for analysis purposes, and towards the end of the project, the data will be stored at SCU-approved and recommended data repositories.

Data will be archived for a period of 15 years after study completion, and this is the maximum recommended period of data archive period by NHMRC ethics requirements guidelines. This period will allow for conducting any follow-up study if the opportunity arises. After that period, electronic data will be securely erased.

### Data analysis

Both descriptive and inferential statistical techniques will be used in this research. In the descriptive analysis, patient characteristics, as well as adherence/wearing time based on the participant’s satisfaction with the footwear and insoles, will be summarised. Under the statistical inference, a paired sample *t*-test will be used to compare the significant difference in plantar pressure between the custom-made footwear and baseline or control footwear. Two independent samples *t*-tests will be applied to compare patient characteristics between low- and high-adherence groups as well as participant’s compliance data and the clinician’s recommended data. In addition, the independent samples *t*-test will be used to compare the demographics and clinical features of the patients admitted to public and private clinics. Furthermore, the Wilcoxon signed-rank test would be used to compare adherence and wearing time between both follow-up moments and baseline. The descriptive and inferential statistical analyses will be performed using IBM SPSS Statistics (version 27). And the statistical significance will be set at *p*<0.05 with a confidence limit at 95% in a two-tailed fashion. For the qualitative data analysis, a thematic analysis will be used, and the software NVivo (version 12) will be utilised for that purpose.

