**Methods:**

This study, involving a series of N-of-1 trials, included 21 participants who had a history of neuropathic plantar forefoot ulcers. Participants were recruited from two public hospitals and one private podiatry clinic in Sydney, New South Wales, Australia. This trial is non-randomised and unblinded. Participants will be recruited from three sites, including two high-risk foot services and a private podiatry clinic in Sydney, Australia. Mobilemat™ and F-Scan® plantar pressure mapping systems by TekScan® (Boston, USA) will be used to measure barefoot and in-shoe plantar pressures. Participants’ self-reports will be used to quantify the wearing period over a certain period of between 2 and 4 weeks during the trial. Participant preference toward footwear, insole design and quality-of-life-related information will be collected and analysed. The descriptive and inferential statistical analyses will be performed using IBM SPSS Statistics (version 27). And the software NVivo (version 12) will be utilised for the qualitative data analysis.

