### Matching and sampling strategies

The participants are their own controls, so all data (plantar pressure data) will be matched within the participants for the intervention and control arms of the study.

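### Reported and recommended wearing time are compared with an independent-samples t-test, although both values belong to the same participant

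*Protocol article*

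**What the plan says.** The Data analysis section names these tests:

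- Pressure in new against control footwear: a paired t-test.
- Adherence and wearing time at follow-up against baseline: the Wilcoxon signed-rank test.
- Adherence groups: "Two independent samples *t*-tests will be applied to compare patient characteristics between low- and high-adherence groups". The same sentence extends these tests to a further comparison, "as well as participant’s compliance data and the clinician’s recommended data".
- Type of clinic: "the independent samples *t*-test will be used to compare the demographics and clinical features of the patients admitted to public and private clinics".

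For all of these, "the statistical significance will be set at *p*<0.05 with a confidence limit at 95% in a two-tailed fashion". The abstract gives the size: "This study, involving a series of N-of-1 trials, included 21 participants". The Outcomes section makes adherence, taken from the self-reported wearing period, part of the secondary outcome. The Sample size section states that no calculation was possible, so the article contains no power figure for any of these tests.

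**The concern.** A participant's reported wear and the wear the clinician recommended to that participant are two values on one person. An independent-samples test treats them as 21 people against 21 other people. It ignores the covariance within the pair and counts 40 degrees of freedom where there are 20 from the differences. Its standard error is right only if the two values are uncorrelated.

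The sentence could also be read as comparing compliance between the low- and high-adherence groups. That would be circular, because the groups are formed from compliance. Worn against recommended is the reading that makes sense.

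What is at stake is the only test in the plan that sets wear against what was prescribed. Adherence is part of the stated aim and a secondary outcome. With 21 participants there is little power to spare.

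Two lesser points arise in the same passage. Adherence enters the analysis of characteristics only as two groups, which discards information if wearing time is recorded as a quantity. And the t-test is the only method named for demographics and clinical features, although the inclusion criteria show that these include unordered categories such as type of deformity.

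**Working it through.** **Inputs from the article:** 21 participants; two-sided 0.05; independent-samples t-test. There is no stated power or error figure to reproduce.

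**Assumptions, not in the article:** within-person correlation ρ from -0.3 to 0.7; SD of recommended wear equal to, half of, or zero times the SD of worn time; true shortfall of 0.5 SD of worn time; normal data.

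**1. The two standard errors.** With n pairs and SDs s₁ and s₂:

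- unpaired: SE² = (s₁² + s₂²)/n, referred to t with 2n − 2 = 40 df (critical value 2.021);
- paired: SE² = (s₁² + s₂² − 2ρs₁s₂)/n, referred to t with n − 1 = 20 df (critical value 2.086).

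They differ by the term 2ρs₁s₂. With equal SDs, the unpaired SE² is 1/(1 − ρ) times the correct one.

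**2. Normal approximation to the true type I error, equal SDs:** 2[1 − Φ(1.96/√(1 − ρ))].

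- ρ = 0.3: 1.96/0.837 = 2.343, giving 0.019
- ρ = 0.5: 1.96/0.707 = 2.772, giving 0.006
- ρ = 0.7: 1.96/0.548 = 3.578, giving 0.0003
- ρ = -0.3: 1.96/1.140 = 1.719, giving 0.086

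**3. Simulation with the t distributions** (100,000 trials per setting, 21 pairs):

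| SD of recommended / SD of worn | ρ | Type I, unpaired | Type I, paired | Power, unpaired | Power, paired |
|---|---|---|---|---|---|
| 1 | -0.3 | 0.086 | 0.049 | 0.37 | 0.27 |
| 1 | 0 | 0.050 | 0.049 | 0.35 | 0.34 |
| 1 | 0.3 | 0.021 | 0.050 | 0.33 | 0.45 |
| 1 | 0.5 | 0.007 | 0.049 | 0.30 | 0.59 |
| 1 | 0.7 | 0.001 | 0.050 | 0.27 | 0.80 |
| 0.5 | 0 | 0.053 | 0.051 | 0.52 | 0.50 |
| 0.5 | 0.5 | 0.015 | 0.050 | 0.52 | 0.71 |

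The higher unpaired power at ρ = -0.3 is not a gain, because it comes with an inflated error rate.

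**4. Same recommendation for everyone (SD zero).** The standard error is then right, but the df are 40 instead of 20. The exact type I error is 2·P(t₂₀ > 2.021) = 0.057. Power is 0.61 unpaired and 0.59 paired, so none is lost.

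**5. Low/high split.** If a characteristic and wearing time truly correlate at 0.5 (assumed), power at n = 21 is about 0.67 with continuous wearing time and 0.44 with a 10/11 split.

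**6. Categorical characteristics.** For a binary feature, the exact type I error of the t-test was enumerated over group splits 11/10, 14/7 and 16/5 and prevalences 0.1, 0.3 and 0.5. It runs from 0.011 to 0.051. Fisher's exact test gives 0.005 to 0.037 in the same settings. For a feature with several unordered categories there is no mean to compare, so the t-test has no meaning.

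**The case against.** The strongest reply is that the harm is not established. The article does not describe the recommended data, and gives neither the correlation nor the SDs. Under positive correlation the unpaired test is conservative, so it would not create false claims. At zero correlation, or with one recommendation for all, it performs almost as well as the paired test. This stands as a limit on the size of the problem. It does not rescue the choice of test: the paired test holds about 5% in every setting, and the unpaired test does not.

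A second reply is that a journal article condenses the full protocol. That protects details left out, but not a test that is named and does not suit its data.

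Several stronger readings are tempting, and the document does not support them:

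- **That the low/high comparison uses the wrong type of test, or has an inflated error rate.** The two groups are different people, so an independent-samples test is the right type. The cut-point may be fixed in a fuller document. A false-positive rate of about 22% arises only if the analyst picks the best of the splits from 5/16 to 16/5, and nothing in the article says so.
- **That t-tests on binary features are invalid.** The computed error stays at or below about 0.05, and Fisher's exact test is more conservative, so it recovers no power. The point survives only for unordered features with several categories.
- **That the plan itself declares wear data to be matched.** The statement "The participants are their own controls" in Matching and sampling strategies refers to plantar pressure data. The case for pairing rests on the structure of the wear data and on the paired tests named in the same paragraph.
- **That the trial's main result is at risk.** The primary pressure comparison is already paired, and wear over time already has a signed-rank test.

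**Conclusion.** The plan names an unpaired test for a within-participant comparison, and this should be corrected. Direction and size are conditional. With equal SDs, the unpaired test is too conservative under positive correlation, about right at zero, and too liberal under negative correlation. The loss can be large: at ρ = 0.5, power for a 0.5 SD shortfall is roughly half that of the paired test. With a constant recommendation the only effect is a type I error of 0.057. These figures rest on the assumed correlations, SD ratios, shortfall and normality. That the data are paired rests only on the natural reading of the sentence.

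The adherence split and the t-test for unordered categories are secondary points, of efficiency and of wording. Severity is moderate: the comparison is secondary and the primary analysis is untouched.

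**What to change.** - **Worn against recommended wear:** compute worn minus recommended wear for each participant. Test it with a paired t-test or the Wilcoxon signed-rank test, and report the estimate with a 95% CI. If the recommendation is the same for all, this becomes a one-sample test of wear against that value.
- **Adherence and characteristics:** where wearing time is recorded as a quantity, relate it to characteristics as a continuous variable (Spearman correlation or regression), in place of or alongside the low/high groups.
- **Categorical characteristics:** limit t-tests to continuous variables. Use categorical methods or description for unordered categories such as deformity type, in both the adherence-group and the public/private comparison.

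The cost is a change of wording in the analysis section. The data, the sample size and the software stay the same.

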### Matching and sampling strategies

The participants are their own controls, so all data (plantar pressure data) will be matched within the participants for the intervention and control arms of the study.

### Plans to give access to the full protocol, participant-level data and statistical code

The full study protocol, de-identified participant-level data and statistical code can be available by contacting the author.

## Oversight and monitoring

### Research governance and ethics

This multisite trial is administered by SCU and NBMLHD HREC and the RGOs of St Vincent’s Hospital Sydney and Nepean Hospital. The ethics have been approved by NBMLHD and the SCU HREC. The approval numbers are 2020/ETH02250 and 2020/093, respectively. The trial is conducted in accordance with the NHMRC guideline [70].

Written informed consent is obtained from each participant by one of the research teams of the respective site at the time of initial assessment and baseline information collection. A copy of the consent form can be available by contacting the corresponding author.

### Trial management and data monitoring committee

The named authors in this article will be part of the trial management committee, which will also include each site-specific investigator and the collaborators reported in the study protocol. The chief investigator will ensure that every co-investigator is actively participating to ensure the participant’s safety and the trial quality is maintained. The lead chief investigator conducts the audit and reviews. Every principal coordinating investigator named in the project protocol for each site will be taking responsibility for the data monitoring.

### Adverse event reporting and harms

Risk in this study relates to the use of new footwear and insoles for the participant.

Participants may face the following risks:Risk of fall or feeling unbalanced with wearing new footwear and insole to start.

Risk mitigation: Participants will be assessed carefully for any potential risk of falls and heel height, and the rocker profile will be adjusted accordingly in the footwear to mitigate the risk of falls or improve balance. At the initial fitting stage, the principal investigator will walk with the participant and will show the appropriate way of walking in the new devices.b.Risk of developing a blister or pressure mark either on the plantar or dorsal surface of the foot and leg. This can be due to changes in volume in the foot or leg for swelling or changes in medications.

Risk mitigation: The principal investigator will ensure that the footwear and insole fit well on the participant’s foot without putting any pressure on the foot and leg. The footwear comes with removable spacer inlays, and the thickness of the insoles can be adjusted if needed. The participants will be given a written wearing information sheet with contact details in case of any emergency and advice to stop wearing them until having a review with any of the investigators.iii.Risk of feeling discomfort or feeling unhappy about wearing a new kind of shoe and insole which may be quite different to what the participant is generally used to. Sometimes, participants may have perceptions that the orthopaedic or therapeutic footwear may not be aesthetically as appealing compared to their regular footwear.

Risk mitigation: The participant will be fully involved in and informed about the process of designing and manufacturing the prescribed footwear and insoles relating to their foot conditions during the first appointment. They will have input on design, style and colour selections for the footwear as per their intended activity. The footwear and insoles for the study will be used from premium orthopaedic brands and manufacturers to ensure the best possible quality and appearance.

### Frequency and plans for auditing trial conduct

This project is subjected to online audit tools of IRMA and REGIS for project progress, and project completion review is conducted yearly or before if the project is shorter than 12 months.

### Plans for communicating important protocol amendments to relevant parties

Any changes that become necessary during the study period will be proposed and amended in the study protocol and be made available to the HREC committee of NBMLHD and SCU. The research governance offices (RGOs) of each study site will also be notified through the Research Ethics Governance Information Systems (REGIS). SCU HREC will be reported through the Integrated Research Management Application (IRMA).

### Dissemination plans

Findings will be published in relevant scientific journals and presented at scientific meetings as well as in a PhD thesis.

## Discussion

A patient-centric study design for footwear intervention in people with diabetes is non-existent [40, 71]. National and international guidelines [35, 72] recommend footwear and insole features to prevent foot ulcer occurrence and recurrence in people with diabetes. They also highlight the importance of adherence to them for improved clinical outcomes, but the guideline on improved adherence is non-existent. Participant satisfaction and adherence to the prescribed footwear are vital to achieving the desired clinical outcome [40].

Footwear is an integral part of the wardrobe for every individual irrespective of gender and activity level. Consideration of participant expectations, geographical and socioeconomic factors, effective education on footwear and activity-specific device designs are important considerations for a personalised-treatment approach for increased adherence [40]. This proposed N-of-1 trial is set to bridge the gap in current clinical practice through evidence-based recommendations to improve offloading efficacy and adherence to the prescribed footwear and insoles in people with diabetes and neuropathy.

### Limitations

The study period is within the COVID-19 restriction in New South Wales, which may affect the study operation and the number of participant recruitment. It may be inconvenient for some potential participants. For example, hospital outpatient department visits require mandatory vaccination for eligible persons and a PCR test conducted within 72 h of the clinic visit.

## Trial status

The trial has been started in two study centres (Western Sydney Podiatry clinic since May 2021 and St Vincent’s Hospital since July 2021). Participant recruitment is expected to be completed by April 2022 in all study centres.

## Definition

Pedorthist: A person who provides medical-grade footwear and/or orthotic appliances and appropriate advice to a patient after assessment and analysis of the patient’s problem(s). This includes the provision of prefabricated footwear, modification of prefabricated footwear, custom-designed and manufactured footwear and/or orthotic appliances and advice on the need and application of medical-grade footwear, orthotic appliances and other footwear.

## Data Availability

The datasets during the study are available from the corresponding author on a reasonable request. All data will be de-identified before making it available to authorised parties.

## Abbreviations

ANOVA: Analysis of variance
CRF: Case report form
PIS: Participant information sheet
HREC: Human Research Ethics Committee
HRFS: High-risk foot service
IRMA: Integrated Research Management Application
NBMLHD: Nepean Blue Mountains Local Health District
NHMRC: National Health and Medical Research Council
PPP: Peak plantar pressure
QOLS: Quality of Life Scale
RDMP: Research Data Management Plan
RGO: Research governance office
SCU: Southern Cross University
